#### Analysis of clinical outcomes

2.13.3

Clinical outcomes will be analysed at the first short term follow-up visit, no more than three months post-randomisation. All QLF images will be rated as good/poor quality by the assessor (blinded to group allocation). Those not judged to be of sufficient quality to accurately generate the outcome variables will be excluded from the analysis. Analysis of the three QLF generated variables will use general linear models, with value of the variable of interest at the first short-term follow-up appointment as the outcome variable, and intervention group allocation as a fixed factor. Baseline value of the variable of interest will be included as a covariate. All analyses will follow the intention to treat principle as far as is practically possible.

Basic Periodontal examination (BPE) scores will be analysed by categorising each patient into one of four outcome categories. 1 – stable healthy (code 0 at baseline and follow-up), 2- stable bleeding (code 1 or greater at baseline and follow-up), 3 – change to bleeding (code 0 at baseline, code 1 or greater at follow-up), and 4 – change to healthy (code 1 or greater at baseline, code 0 at follow-up). The analysis will use multinomial logistic regression to test the effect of intervention group on outcome, with the primary hypothesis of interest between groups 2 and 4.

Multiple imputation analyses will be carried out to investigate the robustness of the results to missing data. Using all the data which is available, including baseline variables, five complete case data sets will be imputed, and each analysed in the same way. The results can then be combined, and compared with the analysis excluding missing data, to assess whether this would be likely to change the overall conclusions.

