*Clinical outcomes*•Change in self-rated oral health between baseline and 6 months post-intervention ‘*Would you say your dental health (mouth, teeth and/or dentures) is? 1*=*very good to 5* = *very poor* [31]•Basic Periodontal Examination (BPE) - clinical data collected by the dentist during the check-up: conversions between codes 1 (bleeding) and 0 (health) between baseline and next dental visit•Change in plaque coverage: percentage of the area of buccal/labial surfaces of anterior teeth calculated from QLF images (Plaque Percentage Index (PPI), ΔR30) [35] taken at baseline and next dental visit. The QLF anterior teeth image will involve a photograph of maxillary and mandibular teeth from canine to canine taken without overlap of incisal edges.•Number of tooth surfaces affected by early caries: Change between baseline and the next dental visit in the number of surfaces which are demineralised on the buccal/labial surfaces of anterior teeth as a proportion of number of surfaces available [35]. Teeth will be cleaned (brushed by the participant after taking the QLF image to measure plaque), before a second QLF image measuring caries.•ΔQ: Change between baseline and the next dental visit in percentage fluorescence loss based on the fluorescence of sound tissue multiplied by the area. This is an estimate of lesion volume, and can be combined over all lesions to give a total estimate of overall severity per patient [35]. Calculated from QLF image taken after cleaning.

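### The main QLF analysis drops patients with a usable follow-up image whenever their baseline image is rejected, which costs precision on three secondary outcomes

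*Protocol article*

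**What the plan says.** All of this is in the protocol article, section 2.13.3 (Analysis of clinical outcomes), unless noted.

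- Grading covers every image, baseline included, and is blind: "All QLF images will be rated as good/poor quality by the assessor (blinded to group allocation".
- Rejected images leave the analysis: "Those not judged to be of sufficient quality to accurately generate the outcome variables will be excluded from the analysis".
- The dependent variable is the follow-up value: "Analysis of the three QLF generated variables will use general linear models, with value of the variable of interest at the first short-term follow-up appointment".
- The model is baseline-adjusted: "Baseline value of the variable of interest will be included as a covariate".
- Imputation has a supporting role: "Multiple imputation analyses will be carried out to investigate the robustness of the results to missing data". Its results are to be "compared with the analysis excluding missing data, to assess whether this would be likely to change the overall conclusions".
- The general principle is: "All analyses will follow the intention to treat principle as far as is practically possible".

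Section 2.8.2 describes the plaque outcome as a change between images "taken at baseline and next dental visit". It also says that plaque is read from an image taken before the participant brushes, and caries from a second image taken afterwards.

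**The concern.** Taken together, these statements make the main QLF analysis a complete-case analysis of covariance. A general linear model cannot use a row with an empty covariate, so a rejected baseline image removes the patient even when the follow-up image is good. Here the baseline serves only to reduce residual variance; randomisation already makes the arms comparable. Discarding an observed outcome because a precision covariate is missing gives up more than the covariate could have added.

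Plaque uses one image and the two caries measures another, so the loss arises separately for each image.

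The QLF sample has little slack. The plaque calculation in section 2.10 uses all 133 patients per group. The only allowance in that section is for refusal of the willingness-to-pay questions. The Discussion cites a similar setting in which 291 of 550 patients (53%) attended both baseline and follow-up.

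**Working it through.** **1. The plan's own figure.** Section 2.10 gives 133 per group, standard deviation 10, difference 3.5 in plaque percentage index, 80% power, α = 0.05 (taken as two-sided).

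Detectable difference = (1.960 + 0.842) × 10 × √(2/133) = 3.44, which agrees with the stated 3.5. Power for 3.5 at 133 per group is 81.4%. The figure reproduces, and it assumes that all 133 contribute.

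**2. Information discarded by complete case.** Let g be the share of baseline images that are gradable, among patients with a gradable follow-up image, and r the baseline to follow-up correlation. In units of 1/variance, a patient with a baseline contributes 1/(1 − r²) and a patient without one contributes 1.

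- Complete case: g/(1 − r²)
- Everyone with a gradable follow-up image, efficiently weighted: (1 − g) + g/(1 − r²)
- Share discarded: (1 − g) / [(1 − g) + g/(1 − r²)]

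Both g and r are assumptions; the protocol states neither.

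| Baselines rejected | r | Calculation | Share discarded |
|---|---|---|---|
| 5% | 0.5 | 0.05 / (0.05 + 0.95/0.75) | 3.8% |
| 10% | 0.5 | 0.10 / (0.10 + 0.90/0.75) | 7.7% |
| 20% | 0.5 | 0.20 / (0.20 + 0.80/0.75) | 15.8% |
| 10% | 0.3 | 0.10 / (0.10 + 0.90/0.91) | 9.2% |
| 10% | 0.7 | 0.10 / (0.10 + 0.90/0.51) | 5.4% |

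The same formulas give the gain over complete case as (1 − g)(1 − r²)/g, which is 4.0%, 8.3% and 18.8% at r = 0.5. Those figures should not be quoted as the share lost.

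**3. Power, by simulation.** Two arms of 133, standard deviation 10, true difference 3.5, 4,000 runs per setting. Images were rejected completely at random and independently at each visit, at the same rate, with no missed visits. Complete case was compared with mean imputation of the baseline plus a missing indicator.

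| r | Rejected at each visit | Complete case | Baseline imputed |
|---|---|---|---|
| 0.3 | 10% | 76.6% | 80.1% |
| 0.3 | 20% | 67.4% | 76.9% |
| 0.5 | 10% | 84.3% | 86.8% |
| 0.5 | 20% | 74.7% | 81.1% |
| 0.7 | 10% | 94.6% | 94.9% |
| 0.7 | 20% | 88.4% | 89.8% |

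Mean estimates lay between 3.46 and 3.53 in absolute value for both methods, so neither was biased.

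**4. Why the gap nearly closes at r = 0.7.** Ordinary least squares with mean imputation weights all patients equally. Its relative variance is g(1 − r²) + (1 − g), against (1 − r²)/g for complete case. At g = 0.90:

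- r = 0.5: 0.775 against 0.833, so 7.0% of the 7.7% is recovered.
- r = 0.7: 0.559 against 0.567, so only about 1.3% of the 5.4% is recovered.

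Mean imputation becomes worse than complete case once 1 − r² falls below g/(1 + g). At g = 0.90 that is 0.474, or r above about 0.73. A constrained longitudinal model weights the two kinds of patient properly and does not have this weakness.

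**The case against.** **This is detail for the analysis plan.** Section 2.13 promises a detailed plan, and a journal article need not say how a missing covariate is handled. That would answer a complaint about silence. But the article itself fixes the exclusion, the covariate and the complete-case status of the main result, so the point concerns a stated method.

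**Imputation is already planned.** It uses all available data and would restore these patients. This limits the harm and stands as mitigation. It does not change which result is the main one.

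**The outcomes are defined as change, so without a baseline nothing was observed.** Section 2.8.2 does use the language of change. The dependent variable in 2.13.3 is the follow-up value, however, and that was observed.

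**A reader might infer bias between arms,** for example if staff in the QLF arm retook poor baseline images because one had to be shown to the patient. The protocol describes no such retaking. Grading is blind, and section 2.7 opens the envelope after the check-up. That section names only BPE as the baseline assessment done beforehand, so the timing of the QLF image is unstated; it is not shown to follow the reveal. If images were affected by allocation, the remedy proposed here would also need defending.

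**A reader might also call this a breach of intention to treat.** The commitment is qualified by practicability, and with blind grading and rejection unrelated to arm the complete-case estimate is unbiased. What remains is lost precision.

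**The effect is small.** This stands. It touches secondary outcomes only, and at a correlation of 0.7 the simulated power gap was about 0.3 to 1.4 points, partly because simple mean imputation recovers little there.

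**Conclusion.** The point holds as a minor, worthwhile improvement. As written, the main analysis of the three QLF outcomes is complete case and discards observed follow-up values when the baseline image is rejected. The demonstrated harm is loss of precision on secondary outcomes. Bias between arms is not shown, and the primary outcome is untouched.

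At r = 0.5 the loss is roughly 4% to 16% of the available information for 5% to 20% of baselines rejected. At 10% rejected it runs from 9.2% (r = 0.3) to 5.4% (r = 0.7). These figures rest on assumed rejection rates and correlations, and on baseline image quality being unrelated to arm and outcome. If few baseline images are rejected, the loss is negligible.

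**What to change.** In the statistical analysis plan, define the main analysis set for each QLF variable as every randomised patient with a gradable follow-up image for that variable. Then use either:

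- a constrained longitudinal model, with baseline and follow-up as responses and a common baseline mean across arms; or
- analysis of covariance with missing baselines imputed without using arm or outcome, for example mean imputation with a missing indicator.

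The first is safer if the correlation may be high, for the reason in step 4 of the working. Keep the complete-case model as a sensitivity analysis, and report by arm the number of baseline and follow-up images rejected.

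Both options assume that baseline images are unaffected by allocation. Confirm, and state, that they are taken before the envelope is opened.

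The cost is a few sentences of plan text and a slightly more complex model. No new data or patient procedures are needed.

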### Randomisation and allocation concealment

2.7

The trial will involve simple randomisation of patients into the three arms in a 1:1:1 ratio. Randomisation will occur just after enrolment by dental staff taking a sequentially numbered envelope. The allocation will be revealed by opening the envelope just prior to the information being given (i.e. by the dentist, witnessed by the dental nurse in the dental surgery, after the check-up has been carried out, including baseline clinical outcome assessment – BPE). The allocation sequence will be drawn up by the trial statistician using computer-generated random numbers with block stratification by each of the four dental practices and random variable block sizes. The trial statistician will be blinded to allocation until the final statistical plan is agreed. The researcher extracting clinical outcome data from QLF photographs (plaque coverage and tooth demineralisation) will also be blind to group allocation, as will the researcher gathering 6 and 12 month follow up data.

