### Predictor and moderator variables

2.9

*Patient socio-demographic characteristics*•Area level deprivation based on home postcode (IMD) [36].•Employment status [36] response from *1*=*employed/self-employed full-time, 2*=*employed or self-employed part-time, 3*=*unemployed at the moment, 4* = *full-time education*•Household income (before deductions e.g. income tax) [37] *according to 9 categories given as weekly or yearly amounts, ranging from 1* = *£0 to 9* = *over £52,000* per *year*•Highest level of education response from *1* = *GCSE/NVQ level 1 or similar, to 5* = *postgraduate degree* [37].•Literacy using the Rapid Estimate of Adult Literacy in Medicine (REALM) [38]. The 8 medical test words, as well as the 3 practice words will be printed and shown to participants on an A4 laminated sheet, but with the American spelling of anemia changed to the English version (anaemia).*Patient dental visiting behaviour, dental anxiety and previous dental experiences*•Dental visiting: *‘In general, do you go to the dentist for: 1*=*a regular check-up, 2*=*an occasional check-up, 3*=*/only when having trouble with my teeth/dentures?’* [31]. *‘How many times have you been to the dentist in the last five years purely for a check-up?’* [31]•Previous pain experience: *‘Have you ever experienced dental pain bad enough to make you go to the dentist (tick all that apply): 1*=*currently in pain, 2*=*In the last 6 months, 3*=*6 months to 2 years ago, 4*=*more than 2 years ago, 5*=*never)’* [31].•Previous experience of dental treatment: *‘Have you ever had fillings/teeth extracted (taken out)/a dental bridge or a tooth crowned/a root canal treatment/a scale and polish?’* [31]•Dental anxiety: The Modified Dental Anxiety Scale (MDAS) [39].*Dental provider characteristics*•Dental practice•Clinician ID delivering information*Oral health*•Number of natural teeth as recorded by the dentist at the check-up*Risk perception and behaviour change predictors/moderators (based on the EPPM model)* [20]•Perceived threat (severity) *‘How serious would it be to you if* [negative outcome] *were to occur,* response from *1*=*not at all serious to 5*=*absolutely serious* Five possible negative outcomes of poor oral health were identified in earlier qualitative work: *‘your teeth were to make you feel uncomfortable when smiling, talking and laughing in front of people; people thought you had failed to look after your own teeth; your teeth were to become more painful and sensitive; you were to need treatment which meant spending more time at the dentist; you were to need treatment which you could not afford’*•Perceived threat (susceptibility) ‘*If you do not follow the dentist's advice, how likely is it that* [same 5 negative outcomes] *will occur*’ response from *1*=*absolutely unlikely to 5 absolutely likely*•Self-efficacy ‘*Please consider how confident you are that you can perform the behaviour properly, regularly and on a long-term basis for* [target behaviour]’ *response* from *1*=*not at all confident to 5*=*absolutely confident*.•Response efficacy ‘[target behaviour] *means I am less likely to have dental problems*’ responses from *1*=*Absolutely disagree to 5*=*Absolutely agree*•Message Fear ‘*How much did the advice you received make you feel … frightened/tense/nervous/anxious/uncomfortable*’ response from *1*=*not at all to 5*=*very much*•Affect regarding threat ‘*How would you feel how if you experienced* [negative outcome] [40]; *and* ‘*How vulnerable would you feel if you experienced* [negative outcome] [41] responses from *1*=*not bad to 5*=*absolutely bad*•Danger control response measured using 3 items: ‘*How likely it will be before your next appointment that you will. 1) follow the advice given by the dentist completely; 2) follow some of the advice given by the dentist 3) talk to someone about the advice the dentist gave you*’ response from *1*=*absolutely unlikely to 5*=*absolutely likely*•Fear control response measured using 4 items with stems: 1) Defensive Avoidance: ‘*I prefer not to think about the advice given to me by the dentist*’ 2) Perceived Manipulation: ‘*The advice given to me by the dentist is untrue or manipulated*’ and 3/4) Message Derogation: ‘*The advice given to me by the dentist is exaggerated*’ and ‘*I do not personally believe the advice given to me by the dentist*’ responses from *1*=*strongly disagree to 5*=*strongly agree*•Intention to change behaviour ‘*Before my next appointment I intend to*.[target behaviour]’ responses from *1* = *absolutely disagree to 5* = *absolutely agree*.

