
### Sample size calculation

2.10

The required sample size calculation is based on a need to detect significant differences in the primary outcome (WTP) between the two interventions (Traffic Light and QLF) and usual care arms at 80% power with α = 0.05. Sample sizes for WTP studies are recognised as difficult, given the problems in deciding on a minimally important difference amongst others [42]. Moreover, for this study, no previous WTP valuations have been undertaken for similar “goods” i.e. information based “goods” in health. In the absence of reliable standard deviation and effect size estimates, sample size was calculated with effect sizes based on numbers of standard deviations rather than absolute numbers. Thus, to detect a difference of 0.5 standard deviations 63 people is calculated to be required per arm. To detect 0.33 standard deviations, 145 per arm would be needed. Accepting a detectable difference between half and a third of a standard deviation and allowing for around 20% refusal to answer WTP questions (protest responses) gives a figure of 133 in each arm or a total sample size of 400. We then calculated the implication of this sample size for the detection of clinical outcome effects, and based this on the secondary outcome of PPI, measured using QLF [35]. Published data on a group of 38 college students showed a mean PPI of 14.8, with a standard deviation of 7.7 [43]. As this is likely to be a more homogenous population than our study, a more conservative estimate of standard deviation of 10 has been used to calculate a sample size of 133 per group would allow us to detect a mean different of 3.5 in PPI between groups, with 80% power, at the 0.05 significance level.

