#### Analysis of behavioural outcomes

2.13.2

Group effects on oral health behaviour between the conditions will be assessed by predicting six and twelve-month follow-up scores from group membership. To minimise the probability of Type 1 error, multivariate analyses will be used. Subsequent univariate analyses will identify specific variables affected by group. Planned comparisons will test the hypotheses that; TL leads to greater positive oral health behaviour change than V, and QLF leads to greater positive behavioural change than V. Separate analyses will examine changes from baseline to 6 months and from baseline to 12 months.

Moderation analyses involve the modelling of two-way interaction effects from the product of the predictor and moderator variables and testing the hypothesis that the interaction term uniquely predicts behavioural change controlling main effects terms [47]. Regression analyses will be used to test this hypothesis. Demographic, dental health and dental visiting variables will be tested as potential moderators.

Mediation analyses assess the extent to which intermediate variables (mediators) explain variance shared between predictor and outcome variables. Again, this analysis will be performed only where between group differences in behavioural change have been identified. Our mediation analysis strategy is based on recommendations by Zhao et al., [48] who specify pre-conditions that the predictor (group membership) be linked to the mediator (EPPM variables), and that the mediator be linked to the criterion (behavioural change) controlling the predictor. When these are established, path analysis can be used to estimate the mediation effect. To statistically test mediation, we will use a bootstrapping method [49]. All potential mediators will be assessed in the same analysis, reducing the likelihood of Type 2 error that would be associated with testing mediators separately.

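### Allocation is stratified by dental practice, but the stated models for the three secondary QLF outcomes omit practice, so their tests are somewhat conservative if practice is prognostic

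*Protocol article*

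**What the plan says.** **Allocation (section 2.7).** The section opens with "The trial will involve simple randomisation of patients into the three arms in a 1:1:1 ratio". It then says that the trial statistician will draw up the sequence by computer "with block stratification by each of the four dental practices and random variable block sizes". The second statement is the operative description: blocked allocation within each practice.

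**QLF outcomes (section 2.13.3).** Plaque coverage, demineralised surfaces and ΔQ are analysed by general linear models. The outcome is the value at the first short-term follow-up visit, "and intervention group allocation as a fixed factor. Baseline value of the variable of interest will be included as a covariate". No other term is listed.

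**BPE (section 2.13.3).** "The analysis will use multinomial logistic regression to test the effect of intervention group on outcome". No covariates are mentioned.

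**Behaviours (section 2.13.2).** Group effects are assessed by "predicting six and twelve-month follow-up scores from group membership". The moderators named there are demographic, dental health and dental visiting variables.

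**Practice is recorded.** Section 2.9 lists "Dental practice•Clinician ID delivering information" under dental provider characteristics, but no model in section 2.13 takes either variable up. Section 2.13 promises a detailed statistical analysis plan, which is not shown.

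**The concern.** Blocking within practice forces the arms to be nearly balanced in each practice, so between-practice differences hardly enter the difference between arms. A model without practice does not know this. It leaves the between-practice variance in the residual and uses it to compute the standard error. The estimate is as precise as the design makes it, but the reported precision is lower: intervals are too wide and the test rejects less often than its nominal level.

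There are reasons why practice could matter for the QLF outcomes. Practice staff take the photographs after training delivered in each practice (sections 2.11 and 2.12). Follow-up is opportunistic at return visits (section 2.12), and the analysed visit may fall up to three months after randomisation (section 2.13.3). What is at stake is modest: precision that the design has already paid for is not reported.

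**Working it through.** **1. The plan's own figure.** Section 2.10 gives, "at 80% power with α = 0.05", a detectable PPI difference of 3.5 with SD 10 and 133 per group. Taking α as two-sided:

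- SE of a difference between two arms = 10 × √(2/133) = 1.226.
- Power = Φ(3.5/1.226 − 1.96) = Φ(0.894) = 0.814.
- Detectable difference at 80% power = (1.96 + 0.842) × 1.226 = 3.44, which the text gives as 3.5.

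The WTP figures of 63 per arm (0.5 SD) and 145 per arm (0.33 SD) also reproduce. The plan's arithmetic therefore holds, and it is the arithmetic of an analysis without practice.

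**2. Effect of leaving practice out.** Let r be the share of the outcome variance, given baseline, that lies between practices. The documents give no value, so r is an assumption shown over a range. SD 10 is taken as the total SD of the analysed outcome. With balance within practice:

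- reported SE (no practice term) = 1.226
- true SE of the estimate = 1.226 × √(1 − r)
- ratio of reported to true SE = 1/√(1 − r)
- true size = 2 × [1 − Φ(1.96/√(1 − r))]
- power without practice = Φ[(3.5 − 1.96 × 1.226)/(1.226 × √(1 − r))]
- power with practice = Φ[3.5/(1.226 × √(1 − r)) − 1.96]

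| Assumed r | SE too large by | True size | Power without practice | Power with practice |
|---|---|---|---|---|
| 0 | 0% | 5.0% | 0.814 | 0.814 |
| 0.01 | 0.5% | 4.9% | 0.816 | 0.818 |
| 0.05 | 2.6% | 4.4% | 0.821 | 0.834 |
| 0.10 | 5.4% | 3.9% | 0.827 | 0.853 |
| 0.20 | 11.8% | 2.8% | 0.841 | 0.891 |

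Worked line for r = 0.10: true SE = 1.226 × 0.949 = 1.163. Without practice, (3.5 − 2.403)/1.163 = 0.943, giving 0.827. With practice, 3.5/1.163 − 1.96 = 1.049, giving 0.853. The difference is 2.6 points.

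**3. Check by simulation.** The set-up was 400 patients in four practices of 100, three arms, permuted blocks of 3 and 6, and 4,000 runs per setting. At r = 0.10 the model without practice reported a mean SE of 1.225, against an actual SD of the estimate of 1.162. The type I error was 0.036 without practice and 0.050 with it; power was 0.826 and 0.853. At r = 0 the two models behaved alike (type I error 0.050 in both, power 0.823 and 0.825), so adding practice when it does not matter costs nothing visible.

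**The case against.** The strongest reply has four parts.

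- **No planned power is lost.** A reader might infer that omitting practice pulls power below the planned 80%. It does not. The calculation in section 2.10 uses an unadjusted SD of 10, and on those inputs the unadjusted analysis has power of 0.81 to 0.83 for r up to 0.10. Only a gain that the protocol never claimed is forgone. This stands.
- **r may be close to zero.** The baseline covariate already absorbs stable differences between practices, and a blinded researcher, not the practices, extracts the QLF variables (section 2.7). At r = 0.01 the gain is about 0.2 points. This stands as a limit on size, not on direction.
- **The BPE and behavioural sentences are not closed lists.** They name a method and the effect to be tested. A reader might infer that practice is excluded there too, but the text does not say so, and the unseen analysis plan may supply covariates. This stands. The QLF sentence is different, because it states the factor and the covariate that the model contains. The linear-model arithmetic also does not carry over directly to BPE: in a multinomial logistic model, omitting a prognostic stratum mainly attenuates the log odds ratio.
- **Simple randomisation is a wording slip.** A reader might infer that the allocation procedure itself is in doubt. It is not, because the same section describes stratified blocks. This stands, and the point is editorial.

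Clinician is also recorded, but allocation was not stratified by clinician, so leaving it out of the models is not a fault.

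**Conclusion.** The point holds for the three secondary QLF outcomes as a small and easily repaired inefficiency. The design stratifies by practice, and the stated models do not use it. If practice is prognostic after baseline adjustment, intervals are somewhat too wide and the tests conservative, by the amounts in the table. That rests on an assumed r, on near balance within practice, and on the protocol's own 133 analysed per group with SD 10.

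Three stronger readings are not supported. The QLF estimates are not biased and their type I error is not inflated; the error is on the conservative side. The sample size does not need to change. The primary WTP comparison is not affected: under section 2.12.1 every participant values all three forms before receiving any information, so the comparison is within patient. Section 2.13.1 also fixes no between-arm model for the revised WTP, only a comparison before and after within the arm received.

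**What to change.** - In section 2.13.3, add dental practice (four levels) as a fixed factor to the general linear models for the three QLF outcomes, beside intervention group and baseline value.
- State the same for the between-arm BPE model (section 2.13.3) and the behavioural models (section 2.13.2), either there or in the statistical analysis plan before the data are analysed.
- In section 2.7, replace the reference to simple randomisation with stratified permuted-block randomisation, so that the label matches the procedure and makes plain why practice belongs in the models.

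The cost is one sentence, one change of wording and 3 degrees of freedom out of about 400. Practice is already recorded, so no new data are needed.

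### The BPE outcome has two definitions: moves between codes 1 and 0 in the outcome list, but all codes of 1 or more pooled against 0 in the analysis, with baseline code and practice left out

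*Protocol article*

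**What the plan says.** Section 2.8.2 (Secondary outcomes, clinical outcomes) defines the BPE outcome as "conversions between codes 1 (bleeding) and 0 (health) between baseline and next dental visit". It names only codes 1 and 0 and covers both directions.

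Section 2.13.3 (Analysis of clinical outcomes) sorts each patient into one of four categories, according to whether the code is 0 or above 0 at each visit. Patients at 0 on both occasions are in category 1. The next group is given as "2- stable bleeding (code 1 or greater at baseline and follow-up". Category 3 holds those who start at 0 and are above it later, and category 4 those who start above 0, at any code, and reach it.

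The analysis is "multinomial logistic regression to test the effect of intervention group on outcome, with the primary hypothesis of interest between groups 2 and 4". No covariate is named for this model.

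For the three QLF variables, the same section uses the follow-up value as the outcome and states: "Baseline value of the variable of interest will be included as a covariate". Section 2.7 stratifies the allocation by practice and records baseline BPE before the allocation is revealed.

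**The concern.** One secondary outcome has two printed definitions, and they differ in who is counted. The words 'or greater' in section 2.13.3 show that codes above 1 are foreseen. Section 2.8.2 gives patients with those codes no place.

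The analysed version has three further features:

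- Any movement that stays above 0 is invisible, whether improvement or worsening.
- Within the pooled group, baseline code is ignored, although it probably predicts strongly who can reach 0.
- Half of each category label (baseline 0 or not) is fixed before allocation, so part of the four-category test concerns baseline status and not the effect of the information given.

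At stake are the meaning and the precision of the BPE result. With two definitions available, there is also a choice of which to report once the data are known.

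**Working it through.** **1. The two definitions side by side**

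| Baseline to follow-up | Section 2.8.2 | Section 2.13.3 |
|---|---|---|
| 1 to 0 | conversion | category 4 |
| 0 to 1 | conversion | category 3 |
| above 1 to 0 | not a 1/0 conversion | category 4 |
| 0 to above 1 | not a 1/0 conversion | category 3 |
| 3 to 1 (improved) | not a 1/0 conversion | category 2, stable |
| 1 to 3 (worsened) | not a 1/0 conversion | category 2, stable |

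The eligible patients differ in any case. The events differ only if codes above 1 can move to 0, or 0 to above 1.

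**2. Does baseline bias the planned contrast?** No. Categories 2 and 4 both require baseline code 1 or more. With arm as the only factor, the multinomial 4-versus-2 part should equal a binary logistic model restricted to those patients. A fit to one simulated data set confirmed this: both models gave arm coefficients of -0.379 (SE 0.385) and 0.079 (SE 0.354).

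**3. What about the overall test?** Three arms and four categories give (3 - 1) x (4 - 1) = 6 degrees of freedom. These split into 2 for category 4 versus 2, 2 for category 3 versus 1, and 2 for baseline 0 versus 1 or more. The last 2 compare the arms on something recorded before allocation. Under randomisation they carry no effect, so they add noise. They do not raise the type I error, because under the null hypothesis the whole label is independent of arm.

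**4. Size of the cost.** The protocol gives no BPE figure to reproduce. Its sample-size figures for willingness-to-pay (63 per arm for 0.5 SD, 145 for 0.33 SD) do reproduce at two-sided 5% and 80% power, but they do not bear on BPE. The inputs below are therefore assumptions, apart from 133 per arm (section 2.10) and the 53% attendance that section 3 cites from another study:

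- 90% of patients have baseline code 1 or more, so n = 133 x 0.9 = 120 per arm, or 133 x 0.53 x 0.9 = 63.
- Improvement by one step is 30% versus 50%.
- Only baseline code 1 can reach 0, and a share q of the pooled group is at code 1.

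The observed rates in the pooled group are then 0.30q and 0.50q. With p̄ their mean and Φ the normal distribution function:

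power = Φ{ [|p1 - p2| - 1.96 √(2 p̄(1 - p̄)/n)] / √([p1(1 - p1) + p2(1 - p2)]/n) }

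For q = 0.5 and n = 119.7, p1 = 0.15, p2 = 0.25 and p̄ = 0.20. Power = Φ{(0.100 - 0.101)/0.051} = 49%. Among code 1 only, n = 59.85 and the rates are 0.30 and 0.50. Power = Φ{(0.200 - 0.176)/0.088} = 61%. Under this premise the higher codes have no events, so a model adjusted for baseline code draws its information on arm from code 1 alone.

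| q | pooled, n = 120 | code 1 only | gain | pooled, n = 63 | code 1 only | gain |
|---|---|---|---|---|---|---|
| 100% | 89% | 89% | 0 | 64% | 64% | 0 |
| 75% | 72% | 79% | 7 | 45% | 51% | 6 |
| 50% | 49% | 61% | 12 | 29% | 37% | 8 |
| 25% | 25% | 35% | 10 | 15% | 20% | 5 |

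**5. Would using the full code be better?** That depends on which codes respond. If every code improved by one step at 30% versus 50% and any step counted, power at n = 120 would be 89% for every q. Simulations at 70 per arm (133 x 0.53) show both sides. If all codes respond, the planned contrast had 35% power and a baseline-adjusted analysis of the code had 69%. If only code 1 responds, the figures were 34% and 18%, so the ranking reverses.

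**The case against.** The strongest defence is that section 2.13.3 makes section 2.8.2 operational. The outcome list names two states, bleeding and health. Patients with higher codes must be classed somewhere, and they are not healthy. A health-versus-bleeding endpoint is a legitimate choice when the first return visit comes at 2–3 weeks. The contrast of interest already conditions on baseline, BPE is one of several secondary outcomes, and a detailed analysis plan is promised.

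Much of this stands. The dichotomy is defensible and the contrast is unbiased. It does not remove the discrepancy, because nothing is left open for a later plan to fill: both definitions are printed and they disagree. If higher codes cannot reach 0 in that time, pooling them only dilutes the contrast. If they can, section 2.8.2 omits those events.

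Two stronger readings are tempting, and the documents support neither:

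- A reader might infer that chance baseline imbalance makes the multinomial test produce false positives. It does not (working, steps 2 and 3).
- A reader might infer that the plan discards most of the information and that an ordinal model is plainly superior. The protocol gives neither a BPE distribution nor the share of patients above code 1. High or medium risk can also come from caries or from patient factors such as smoking, so it does not imply high BPE codes. Step 5 shows that the ranking can go either way.

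**Conclusion.** The point holds as a conflict of definitions plus an avoidable inefficiency. Sections 2.8.2 and 2.13.3 give the same secondary outcome different eligible patients and, if higher codes can reach 0, different events. The 2-versus-4 contrast is valid, but it ignores baseline code and the stratifying practice and counts movement above 0 as stable. The overall four-category test is valid but carries pre-allocation status as noise.

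In the illustration, ignoring baseline code costs about 5 to 12 points of power when 25% to 75% of the pooled group is at code 1, and nothing when all are. This rests on assumed rates, an assumed 90% at code 1 or more, and the premise that only code 1 reaches 0. The true cost cannot be derived from the protocol. The primary outcome and the sample size are not touched.

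**What to change.** 1. Reconcile sections 2.8.2 and 2.13.3 to one definition that says explicitly how codes above 1 are treated.
2. Replace the four-category outcome with follow-up status (0 versus 1 or more). Model it by logistic regression on arm, baseline BPE code and practice, with the main comparison among patients with baseline code 1 or more. Patients at code 0 at baseline then form a separate, secondary comparison.
3. Report conversion to 0 among patients with baseline code 1 separately.
4. If wanted, add a baseline-adjusted ordinal analysis of the follow-up code as supporting only, since its power relative to the main analysis depends on whether codes above 1 respond.

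The cost is a wording change and slightly more modelling, using data already collected. Cells may be sparse at higher baseline codes. If no patient there reaches 0, the term for that code cannot be estimated, so the plan should state in advance how such codes will be grouped.
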